### Blinding

This trial is a single blind study: both the researchers (outcome assessors and statistical analysts) and participants are blinded to the group assignment and the blindness will never be broken prior to the completion of study unless adverse events happen. But for clinicians or therapists administering at the intervention protocol, it is impossible for them to be blinded. Meanwhile, the randomized sequence of allocation will be replaced by some unrelated codes, such as A and B. In this study, code A means active group and code B means control group. Each parameter of randomization will be kept in a special sealed opaque envelope.

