### Safety assessments

During the whole period of intervention, any adverse events (i.e., cannot tolerate MRI procedures, headache, or any discomfort triggered by rTMS stimulation, decreased sleep quality, and seizures) will be recorded per session after intervention immediately. In addition, spontaneous reporting is also requested if there are any abnormalities or adverse events happened during the trial. To ensure safety, the TMS operator should be familiar with the trial scheme and procedure, and all procedures that are related to safety and ethical considerations will follow the guidelines of TMS application strictly [11]. Whenever adverse event happens during the interventional period, the participants will get related medical care accordingly. In addition, all details will be recorded and reported to primary investigator and the Ethic Committee to decide whether the subject is appropriate to continue the trial. All adverse events collected will be truthfully reported in future trial publications and the incidence of adverse events will also be considered into analysis.

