### Data collection and management

At first, the screeners will ensure the inclusion and exclusion criteria and collect basic characteristic data before the randomization and allocation. The trained outcome evaluators, who are blinded to the assignments and not engaged in the intervention, play an important role in measurements of primary and secondary outcomes. Then, the data of all participants will be entered into the designed Case Report Forms (CRF). Besides, each CRF will be checked twice to ensure the accuracy and completion of data collection throughout the study. Meanwhile, all related documents will be coded by specific identification codes and kept in locked boxes to protect participants’ privacy and data security. Furthermore, the MRI scans and biological indicators will be stored on a locked computer with a password that only the primary researcher knows. According to the rules of medical files preservation and principle of Good Clinical Practice (GCP), these materials will be preserved for 5 years after completion of this trial.

In addition, this trial will be monitored for safety control by a physical therapist and two clinical physicians who have no direct involvement in the study. They will be responsible for ensuring the training of standard operation procedure (SOP), monitoring study progress, reviewing all adverse events on a weekly basis, and discontinuing the study if the data raises sufficient concern (e.g., interventions cause treatment site discomfort and headache). All adverse events will be reported to DSMB and to the Ethic Committee of Affiliated Rehabilitation Hospital of Fujian University of Traditional Chinese Medicine by the study evaluators.

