### Statistical analysis

All statistical analyses of non-imaging data will be conducted using SPSS Version 25 by an independent statistician who is blinded to the labeling of active and sham groups. The statistical significance level of test is established at 0.05, two-tailed. In the process of data analysis, continuous variables will be represented using mean, standard deviation, maximum or minimum according to the statistical distribution, and the categorical data will be presented by percentage. To verify the efficacy of our intervention, comparison of all outcomes which are categorized as continuous variable and shown in mean scores will be included into analysis by independent sample t test or non-parametric test (Mann-Whitney *U* test). Moreover, both analysis within group and between groups after 4-week intervention will be carried to observe the difference of these two interventional methods. If necessary, logistic regression, general linear correlation or regression will be taken into consideration between different types of outcomes. Similarly, according to the type and distribution of variables, the comparison of basic data between the active group and sham rTMS group will be performed using Student’s *t* test, chi-squared test, or nonparametric test. Furthermore, the participants who drop out during the intervention period will not be excluded due to the principle of Intention to treat (ITT) and the missing data will be replaced by last observation carried forward rules.

The hypothesis of this trial is that the active stimulation group shows greater changes than the sham stimulation group. Therefore, the main analysis is the comparison of changes between groups, measured at baseline and at the end of intervention. If significant differences are observed after intervention and no significant difference is observed at the baseline, we may conclude the efficacy of rTMS to individuals with high level of perceived stress.

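### The protocol prints the meaning of its group codes, which defeats analyst masking, and its open adverse-event exception leaves assessor and participant blinding unprotected

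*Protocol article*

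**What the plan says.** The Blinding section of the protocol article states who is masked: "both the researchers (outcome assessors and statistical analysts) and participants are blinded to the group assignment". Only the staff who deliver the stimulation are excepted. The device for masking is a code: "the randomized sequence of allocation will be replaced by some unrelated codes, such as A and B". The next sentence says what the codes stand for: "In this study, code A means active group and code B means control group".

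The Statistical analysis section assigns the non-imaging analyses to "an independent statistician who is blinded to the labeling of active and sham groups". The Discussion concedes that therapists cannot be masked and offers the masking of evaluators and statisticians for the whole trial as the protection against bias.

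The Blinding section also contains an exception: "the blindness will never be broken prior to the completion of study unless adverse events happen". The Safety assessments section lists among adverse events "headache, or any discomfort triggered by rTMS stimulation, decreased sleep quality, and seizures", to be recorded after each session.

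**The concern.** A code masks the analyst only while its meaning is unknown to the analyst. Here the meaning is printed in the document that an analyst would be expected to read. The protocol as shown leaves the analyst some judgement, such as a t test or a Mann-Whitney test, and regression if thought necessary. An analysis plan that is not shown may settle these points. Until it does, masking is what prevents such choices from being guided by the result. The Discussion also presents statistician masking as part of the answer to an acknowledged weakness, so losing it weakens the trial's own defence.

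The exception raises a separate problem. Read literally, a mild headache is enough to permit a break of the blind, and the text sets no limit on whose allocation is revealed or to whom. The primary outcome, the PSS-14, is completed by participants themselves at the end of the intervention, so a break that reached a participant during treatment could affect the answers.

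**Working it through.** The documents give no figure for this point, so the check is mainly a comparison of passages.

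**1. Is the code a mask?** The Blinding section intends codes unrelated to the arms. The following sentence fixes the relation for this study. The words *such as* before A and B do not help, because that sentence then commits to A and B. Nor does keeping randomization details in sealed envelopes, since the key is in the text. A file with groups labelled A and B is open to any reader of the section, which contradicts "both the researchers (outcome assessors and statistical analysts) and participants are blinded to the group assignment" as regards analysts, and "by an independent statistician who is blinded to the labeling of active and sham groups".

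**2. How many labels are affected?** There are two codes and the key gives both. With 20 participants per arm, 20 + 20 = 40, so all 40 labels can be decoded.

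**3. How wide is the adverse-event exception?** The Blinding section makes the occurrence of adverse events the only condition. It sets no limit by participant or by recipient of the code. The Safety assessments section includes minor events and records them per session: 12 sessions × 40 participants = up to 480 recording occasions, all within the intervention period.

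The documents give no event rate. As an illustration, assume that each participant independently has probability *p* of at least one qualifying event. The chance that at least one of the 40 does is 1 − (1 − *p*)^40:

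| Assumed *p* | Expected participants with an event (40*p*) | Chance of at least one |
|---|---|---|
| 2% | 0.8 | 55% |
| 5% | 2 | 87% |
| 10% | 4 | 98.5% |
| 20% | 8 | over 99.9% |

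The condition would probably be met at least once. This is the chance that a break becomes permissible, not the chance that one takes place. With one code per arm, a single break also tells anyone who sees the codes the arm of everyone who shares that code.

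**4. Are assessors shown to be unmasked?** No. The Data collection and management section says that evaluators are masked and do not deliver treatment, and that study documents carry identification codes. Nothing says that these show A or B. The section has study evaluators do the reporting ("All adverse events will be reported to DSMB"), but reporting an event does not disclose an arm.

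**5. Is participant blinding consistent elsewhere?** No. The Randomization and allocation concealment section has the therapist and all eligible participants told the allocation result by telephone, whereas the Blinding section says that participants are blinded. Both statements cannot stand.

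**The case against.** The strongest reply is that the article condenses a fuller protocol, that code-break procedure commonly sits there, and that the exception permits a break rather than requiring one. The Safety assessments section describes what follows an event: care, recording, and a report to the primary investigator and the ethics committee. The Data collection and management section adds weekly review by three people without direct involvement in the study. Neither includes an unblinding step. This stands, and it limits the second part of the point to loose wording. It does not answer the first part: the article did not leave the key out, it disclosed it.

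Stronger readings are tempting, but the documents do not support them:

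- A reader might infer that assessor blinding has failed. No section says that assessors see the A/B code or are told of a code break.
- A reader might infer that every adverse event unblinds the participant. The text only allows a break.
- A reader might infer that breaks would fall mainly on the active arm and try to count them by arm. There are no event rates by arm, and the Sham rTMS group section describes a sham coil with similar noise and tactile sensation.
- A reader might add that the analyst is free to choose between change scores and post-treatment scores. The Statistical analysis section names the comparison of changes as the main analysis.

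**Conclusion.** The statement of the key is wrong as written. It contradicts the analyst blinding claimed in two sections and relied on in a third, and it covers all 40 labels. This rests on two modest assumptions: that the analysis file uses the A/B labels as the text says, and that the analyst has read the protocol.

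The adverse-event exception is too open. It leaves assessor and participant blinding unprotected without showing that either is lost. The illustrative chances of 55% to over 99.9% that the condition is met at least once depend on assumed participant event rates of 2% to 20%.

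No bias in the treatment effect can be computed from the documents. The correction should be made because masking is the trial's stated protection and the change costs almost nothing.

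**What to change.** 1. Delete the sentence that gives the meaning of A and B. Deletion alone is not enough, since the key has been published, so also issue new arbitrary group labels for the analysis file.
2. Name a key holder who is explicitly not the analyst. The Randomization and allocation concealment section and the Statistical analysis section each refer only to an independent statistician and do not say that these are different people. The one who generated the sequence may hold the key only if someone else does the analysis. Release the key only after database lock and completion of the primary analysis.
3. Reword the exception so that any code break applies to the individual participant only, is logged with date and reason, and leaves outcome assessors and analysts masked. The clinical grounds for a break are for the investigators to set.
4. In the same edit, reconcile the telephone notification of participants with the statement that they are blinded.

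The cost is one relabelled file and a few sentences, with no effect on sample size, visits or data collected. Recruitment was still under way when the article was submitted, so the change could be made before analysis.

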### Data collection and management

At first, the screeners will ensure the inclusion and exclusion criteria and collect basic characteristic data before the randomization and allocation. The trained outcome evaluators, who are blinded to the assignments and not engaged in the intervention, play an important role in measurements of primary and secondary outcomes. Then, the data of all participants will be entered into the designed Case Report Forms (CRF). Besides, each CRF will be checked twice to ensure the accuracy and completion of data collection throughout the study. Meanwhile, all related documents will be coded by specific identification codes and kept in locked boxes to protect participants’ privacy and data security. Furthermore, the MRI scans and biological indicators will be stored on a locked computer with a password that only the primary researcher knows. According to the rules of medical files preservation and principle of Good Clinical Practice (GCP), these materials will be preserved for 5 years after completion of this trial.

In addition, this trial will be monitored for safety control by a physical therapist and two clinical physicians who have no direct involvement in the study. They will be responsible for ensuring the training of standard operation procedure (SOP), monitoring study progress, reviewing all adverse events on a weekly basis, and discontinuing the study if the data raises sufficient concern (e.g., interventions cause treatment site discomfort and headache). All adverse events will be reported to DSMB and to the Ethic Committee of Affiliated Rehabilitation Hospital of Fujian University of Traditional Chinese Medicine by the study evaluators.

### Statistical analysis

All statistical analyses of non-imaging data will be conducted using SPSS Version 25 by an independent statistician who is blinded to the labeling of active and sham groups. The statistical significance level of test is established at 0.05, two-tailed. In the process of data analysis, continuous variables will be represented using mean, standard deviation, maximum or minimum according to the statistical distribution, and the categorical data will be presented by percentage. To verify the efficacy of our intervention, comparison of all outcomes which are categorized as continuous variable and shown in mean scores will be included into analysis by independent sample t test or non-parametric test (Mann-Whitney *U* test). Moreover, both analysis within group and between groups after 4-week intervention will be carried to observe the difference of these two interventional methods. If necessary, logistic regression, general linear correlation or regression will be taken into consideration between different types of outcomes. Similarly, according to the type and distribution of variables, the comparison of basic data between the active group and sham rTMS group will be performed using Student’s *t* test, chi-squared test, or nonparametric test. Furthermore, the participants who drop out during the intervention period will not be excluded due to the principle of Intention to treat (ITT) and the missing data will be replaced by last observation carried forward rules.

The hypothesis of this trial is that the active stimulation group shows greater changes than the sham stimulation group. Therefore, the main analysis is the comparison of changes between groups, measured at baseline and at the end of intervention. If significant differences are observed after intervention and no significant difference is observed at the baseline, we may conclude the efficacy of rTMS to individuals with high level of perceived stress.

In addition, the left and right side of DLPFC will be set as the seed regions for the analysis of the structural and functional MRI data to examine the longitudinal neural changes and to explore the relationship between the brain plasticity and perceived stress caused by the stimulation. Specifically, the gray matter density in bilateral DLPFC, the functional connectivity with the DLPFC as seed, and task activation will be calculated using statistical parametric mapping software (SPM12, Welcome Department of Cognitive Neurology, London, UK, http://www.fil.ion.ucl.ac.uk/spm/). A two-factor repeated measures ANOVA (group factor for active and sham groups, and two longitudinal measures at baseline and after intervention) will be conducted on the gray matter density, functional connectivity, and the task activation separately. Further correlational analyses will be performed between the imaging and the psychological and biological measures to explore the relationship between brain and perceived stress.

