**Method:**

This is a single blinded, randomized sham-controlled trial, targeting at young healthy adults aging from 18 to 24 years old. Forty eligible volunteers will be recruited and randomly divided into active and sham rTMS group. All subjects will take a set of neuropsychological and biological assessments and MRI scanning before and right after the intervention. During the interventional period, 12-session stimulations will be performed in 4 weeks with three sessions per week. The primary outcome will detect the difference of Chinese 14-item perceived stress scales between active and sham rTMS groups after intervention. Secondary outcomes will examine the differences of other affective measurements, level of cortisol, and MRI-derived neural functional measures between the two groups after intervention.

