### Primary outcome measurement

The primary outcome is the change in perceived stress levels, which is measured by Chinese 14-item perceived stress scales (PSS-14) [28]. The PSS consists of 14 items (7 positive items and 7 negative items) and is a widely used psychological scale to observe the perception of stress in different situation [29]. Participants are required to complete all questions that indicated their perceived stress level within the past several months. Each item is rated on a 5-point scale ranging from 0 (means never) to 4 (means very often), whereas the higher scores indicate higher stress level [30, 31]. Data will be collected at the baseline assessment and the end of intervention (4 weeks after randomization). The mean scores will be calculated for the subsequent statistical analyses.

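### The primary PSS-14 comparison is valid but takes no account of baseline PSS-14 as a covariate, so it gives up precision and handles chance baseline imbalance poorly

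*Protocol article*

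**What the plan says.** The Statistical analysis section sends all continuous outcomes, PSS-14 among them, to a two-sample comparison: they "will be included into analysis by independent sample t test or non-parametric test", the latter being the Mann-Whitney U test. It then states that "the main analysis is the comparison of changes between groups, measured at baseline and at the end of intervention". Significance is judged at 0.05, two-sided.

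The Primary outcome measurement section agrees with the change-score reading: "The primary outcome is the change in perceived stress levels". Two other places point to post-intervention scores. The abstract's Method paragraph says "The primary outcome will detect the difference of Chinese 14-item perceived stress scales between active and sham rTMS groups after intervention". The rule for concluding efficacy begins "If significant differences are observed after intervention and no significant difference is observed at the baseline".

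Baseline PSS-14 is available for everyone: "Data will be collected at the baseline assessment and the end of intervention (4 weeks after randomization"), and the Inclusion procedure section places the baseline scales before randomization. The only regression mentioned for non-imaging data is optional and has another purpose: "general linear correlation or regression will be taken into consideration between different types of outcomes". That relates outcomes to one another. It does not adjust the PSS-14 comparison for its own baseline.

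**The concern.** With 20 participants per arm, the difference in mean baseline PSS-14 has a standard error of about a third of an SD, so imbalances too small to be significant but large enough to move the estimate will sometimes occur. A post-score comparison carries a share r of the imbalance into the estimate. A change-score comparison subtracts all of it when only a share r should go, and so errs by a share (1 − r) in the other direction. ANCOVA estimates the share from the data.

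The condition of no significant baseline difference shows that imbalance is on the authors' minds, but it is a gate and not an adjustment. It does nothing about imbalances below the threshold. Under proper randomization it fails by chance about 5% of the time, and the article does not say what happens then.

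At stake is precision in a small trial, and an estimate that can be defended in the one trial actually run. A further benefit is that, with baseline as a covariate, the estimated group effect is the same whether the response is the post score or the change. The difference in wording between abstract and analysis section then no longer affects the result.

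**Working it through.** **Inputs from the protocol (Sample size calculation).** Post-treatment HDRS-17: active 7.70 (SD 4.34, n = 10), sham 12.29 (SD 4.50, n = 7); target d = 1.04; two-sided α = 0.05; power 80%; N = 32 evaluable; 20% dropout; 40 enrolled.

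**Assumed.** Correlation r between baseline and end-of-intervention PSS-14 of 0.3, 0.5 or 0.7 (the protocol gives none); equal SDs at both times; d = 1.04 on the post-score SD.

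**1. The plan's own figure.** d = (12.29 − 7.70)/√((4.34² + 4.50²)/2) = 4.59/4.42 = 1.038. The noncentral-t calculation for an unadjusted two-sided t test gives 16 per arm, or 32, with 81.2% power; 32/0.80 = 40. The stated sample size reproduces.

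**2. Variance of the three analyses, relative to post scores.** Post: 1. Change: 2(1 − r). ANCOVA: 1 − r². The ratio of change to ANCOVA is 2/(1 + r).

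| r | change | ANCOVA | change/ANCOVA |
|---|---|---|---|
| 0.3 | 1.40 | 0.91 | 1.54 |
| 0.5 | 1.00 | 0.75 | 1.33 |
| 0.7 | 0.60 | 0.51 | 1.18 |

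**3. Power.** Effective effect sizes are 1.04/√(2(1 − r)) for change and 1.04/√(1 − r²) for ANCOVA, the latter with one degree of freedom fewer.

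| r | n per arm | change | post | ANCOVA |
|---|---|---|---|---|
| 0.3 | 16 | 67% | 81% | 85% |
| 0.5 | 16 | 81% | 81% | 91% |
| 0.7 | 16 | 96% | 81% | 98% |
| 0.3 | 20 | 77% | 89% | 92% |
| 0.5 | 20 | 89% | 89% | 96% |
| 0.7 | 20 | 99% | 89% | 99% |

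The rows for 20 per arm matter because the plan keeps dropouts by carrying the last observation forward; they ignore any dilution this causes.

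The ANCOVA formula treats the slope as known. Estimating it multiplies the variance by about 1 + 1/(32 − 4) = 1.036, which at 16 per arm lowers ANCOVA power to 83%, 90% and 97%. The ordering in the table is unchanged. Strictly, ANCOVA then beats post scores when r² > 1/29 (r above about 0.19) and change scores when 1 + r < 56/29 (r below about 0.93).

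**4. Effect of a chance imbalance.** With 20 per arm, the SE of the baseline difference is √(2/20) = 0.32 SD. An imbalance of that size shifts the post-score estimate by 0.32r, or +0.09 to +0.22 SD for r from 0.3 to 0.7. It shifts the change-score estimate by −0.32(1 − r), or −0.22 to −0.09 SD. Under a linear model ANCOVA has no such shift.

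**5. Type I error.** I simulated 200,000 null trials for each r, with 20 per arm. Overall error is 5% for all three methods. Among the 14% of trials with a baseline difference beyond 1.3 standard errors that is still non-significant, it is about 7% to 10% (change), 6.5% to 11.5% (post) and 5% (ANCOVA). Among all trials that pass the no-significant-baseline-difference condition, it is slightly below 5% for change and post.

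**6. Effect of the entry cut-off.** Entry requires PSS-14 above 25. Selection on baseline leaves the regression slope b unchanged and shrinks the baseline variance v. The change-to-ANCOVA ratio becomes 1 + (1 − b)²v/(1 − b²). For illustration, take normal scores cut at the population mean, so v = 1 − 2/π = 0.363. Then b = 0.3, 0.5 and 0.7 give 1.20, 1.12 and 1.06, against 1.54, 1.33 and 1.18 in step 2.

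**The case against.** The strongest reply is that nothing here is an error. A randomized comparison of change scores is a legitimate analysis, the sample size reproduces, and the abstract calls the study exploratory. This stands, and it limits the point to an improvement in efficiency.

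A reader might go further in four ways that the protocol does not support:

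- **Baseline imbalance is ignored.** This fits only the post-score wording in the abstract and the efficacy rule. The stated main analysis subtracts baseline, so the fault there is over-correction.
- **The false-positive rate is inflated.** It is not: overall error is 5%. The higher figures in step 5 belong to a selected 14% of null trials and are offset by lower error in the rest.
- **The PSS-14 cut-off is where change scores do worst.** A lower correlation under restricted range suggests this, but the equal-SD ratio no longer applies. With the slope fixed and baseline variance reduced, the penalty shrinks (step 6).
- **The trial is underpowered as a result.** With 16 per arm, change scores fall below the planned 80% only if r is under about 0.5. At r = 0.8 the comparison is 99.4% against 99.7%.

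It can also be said that the trigger for choosing Mann-Whitney over the t test is normally left to a full analysis plan. That is fair, and its absence is not counted here. The choice of an unadjusted two-sample test is different, because the article itself makes it.

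**Conclusion.** The point holds as a recommended improvement. The article fixes an unadjusted two-sample test for PSS-14 although a baseline value is collected on every participant. That test is valid, but less precise than ANCOVA over the range of r considered, and neither change nor post scores deal properly with the imbalance that happens to arise. The condition on baseline significance does not substitute for adjustment.

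The size depends on r, which is assumed. At 16 per arm the gain over change scores is about 18 percentage points of power at r = 0.3 (67% to 85%), 10 at r = 0.5 (81% to 91%) and 2 at r = 0.7 (96% to 98%). At 20 per arm it is about 15, 7 and under 1. These figures rest on equal SDs and on d = 1.04 applied to post scores. Because the entry cut-off narrows the baseline range, the true gain over change scores may be smaller. No conclusion of invalid inference or an inadequate sample size follows.

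**What to change.** State the primary analysis as a linear model of end-of-intervention PSS-14 on group and baseline PSS-14, reporting the adjusted mean difference with its 95% confidence interval. Use the same model for DASS, CAS and serum cortisol, each with its own baseline. Keep the Mann-Whitney test as a sensitivity analysis only. Remove the condition that baseline must not differ significantly before efficacy can be concluded.

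The cost is one sentence in the analysis section and one degree of freedom. No extra data, participants or software are needed, since SPSS fits the model. Recruitment was still under way when the article was submitted, so the change should be recorded as a dated amendment before unblinding.

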### Sample size calculation

We aim to investigate the efficacy of the technique of rTMS for improving cognitive emotional control in high-level perceived stress individuals. Since there are no studies of the rTMS efficacy on perceived stress, we have referred to related literature that investigated the effect of rTMS on depression [37], and the sample size estimation was based on the improvement of Hamilton Depression Rating scale (HDRS-17) scores. According to a previous study [37], the mean and its SD of HDRS-17 scores after a 4-month active rTMS intervention (10 subjects included) for treatment-resistant depression were 7.70 and 4.34, respectively, whereas they were 12.29 and 4.50 in the sham rTMS group (7 subjects included), respectively, resulting an effect size (Cohen’s *D*) of 1.038. Referencing from these, a sample size of 32 participants was calculated to sufficiently detect the target effect size (1.04) with a type I error of 5% (*α* = 0.05) and 80% power (*β* = 0.20) by Gpower V.3.1.9.2 software. However, to overcome a dropout rate of 20%, we increased the number of enrollments and finally 40 participants will be allocated randomly into the active and sham stimulation groups with 20 participants in each group for the completion of this trial.

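### With PSS-14 measured only at baseline and week 4, last observation carried forward gives everyone without a week-4 score a change of exactly zero, and the sample size does not allow for the dilution

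*Protocol article*

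**What the plan says.** Under Primary outcome measurement, the article schedules PSS-14 twice: "Data will be collected at the baseline assessment and the end of intervention (4 weeks after randomization"). No interim PSS-14 is described.

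Under Statistical analysis, the main analysis is the between-group comparison of change from baseline to the end of intervention, by t test or Mann-Whitney test. Participants who drop out stay in under intention to treat, and "the missing data will be replaced by last observation carried forward rules". No other missing-data method and no sensitivity analysis is named.

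Under Sample size calculation, "a sample size of 32 participants was calculated" for a standardised effect of 1.04 with 80% power. Then, "to overcome a dropout rate of 20%, we increased the number of enrollments", giving 40 in total and 20 per arm.

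**The concern.** With a single earlier measurement, carrying the last observation forward is the same as carrying baseline forward. The rule does not estimate the missing week-4 score; it enters no change as though it had been observed. Baseline is also a doubtful stand-in here. Entry requires a PSS-14 score above 25, so some fall by regression to the mean is plausible in both arms, and a sham response may add to it.

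Two things are at stake. The estimated effect shrinks toward zero as dropout rises, or moves in either direction if dropout differs between arms. And the stated power belongs to a different calculation, in which those lost simply leave and those remaining show the full effect.

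**Working it through.** **Inputs from the article.** Means 7.70 and 12.29, SDs 4.34 and 4.50; target effect 1.04; two-sided alpha 0.05; 80% power; 32 participants raised to 40; 20% dropout; 20 per arm.

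**Assumptions not in the article.** The effect of 1.04 is read as a difference in mean PSS-14 change with SD of change equal to 1. (The article takes 1.04 from post-treatment depression scores.) All dropouts lack a week-4 score. Mean improvement in the sham arm, μS, is 0, 0.5 or 1 SD.

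**1. The plan's own figure.**
- d = (12.29 − 7.70) / √((4.34² + 4.50²)/2) = 4.59 / 4.42 = 1.038, as stated.
- Two-sided t test with d = 1.04: 15 per arm gives 78.5% power and 16 per arm gives 81.2%, so 32 in total. Then 32 / 0.8 = 40.
- The sample size is correct on its own inputs, and its logic is that 16 observed per arm carry the full effect.

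**2. Effect estimate under the stated rule.** With a fraction q missing and set to zero, an arm's expected mean change is (1 − q)μ. With equal q the difference is (1 − q)(μA − μS) = 0.8 × 1.04 = 0.832 SD. This does not depend on μS. At 10% dropout it is 0.9 × 1.04 = 0.936 SD.

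**3. Power under the stated rule, 20 per arm.** With random dropout the variance in an arm is (1 − q) + q(1 − q)μ². For μS = 0 and q = 0.2:
- sham: 0.8
- active: 0.8 + 0.16 × 1.04² = 0.973
- effective d = 0.832 / √((0.8 + 0.973)/2) = 0.884, power 77.7%

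The same steps give effective d of 0.828 (72.3%) at μS = 0.5 and 0.755 (64.4%) at μS = 1. Simulation of the t test agrees closely:

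| Sham improvement | 20% dropout, random / exactly 4 per arm | 10% dropout, random / exactly 2 per arm |
|---|---|---|
| 0 SD | 78.5% / 79.7% | 85% / 85% |
| 0.5 SD | 72.3% / 74.9% | 82% / 83% |
| 1 SD | 63.9% / 67.1% | 77% / 80% |

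By the analytic formula, keeping the rule at 20% dropout would need 44, 48 or 58 participants for 80% power at 0, 0.5 or 1 SD.

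**4. Unequal dropout.** The expected difference is (1 − qA)μA − (1 − qS)μS. Take μS = 1 and a true difference of 1.04, so μA = 2.04:
- 30% active, 10% sham: 0.7 × 2.04 − 0.9 × 1 = 0.53 SD
- 10% active, 30% sham: 0.9 × 2.04 − 0.7 × 1 = 1.14 SD, above the truth

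With no true effect and 1 SD improvement in both arms, 10% active and 30% sham dropout gives 0.9 − 0.7 = 0.2 SD. The simulated two-sided type I error is 7.9% with fixed counts and about 10% with random dropout. At 0.5 SD improvement the spurious difference is 0.1 SD and the fixed-count error is about 6%.

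**The case against.** Four points can fairly be made for the plan.

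- **Scope.** A reader might infer that every dropout is set to zero. The article does not support that. The Withdrawal or dropout criteria stop the intervention; they do not say that assessment stops. Someone who leaves stimulation but completes the week-4 form is unaffected. Whether such forms are sought is a detail that an article may leave to the full protocol, so its absence is no fault. This stands, and the point is limited to participants without a week-4 score.
- **Power.** A reader might infer that the 80% is plainly lost. With no sham improvement and equal 20% dropout, the shortfall is under 2 points by simulation. The 20% is also a planning allowance, and at 10% dropout power stays near or above 80% in most of the cases shown. This stands too: the loss is conditional.
- **Type I error.** Nothing in the article predicts a threefold imbalance in dropout, and participants are blinded with a sham coil described as indistinguishable. The 8–10% illustrates what the rule can do and is not a forecast.
- **Contradiction.** One might read the sample-size and analysis sections as contradicting each other. They do not in words: the sample-size section never says that dropouts leave the analysis. What is missing is an allowance for the dilution that the analysis rule brings.

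None of this touches the mechanism. The rule is stated, the two assessment times are stated, and together they fix the missing changes at zero.

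**Conclusion.** The point holds for participants without a week-4 PSS-14 score. The mechanism follows directly from the article. The attenuation from 1.04 to about 0.83 SD follows by arithmetic from the plan's own 20% dropout, if dropout is equal between arms and all dropouts lack a week-4 score.

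The power figures are less certain. They run from about 80% down to 64% at 20% dropout and from 85% to 77% at 10%, and the position in each range rests on a sham response that the article does not give. Some sham improvement is plausible given selection on a high score, but its size is unknown. With equal dropout the error is toward no effect. It cannot be called conservative in general, because unequal dropout can push the estimate above the truth or create a difference where there is none.

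**What to change.** In Statistical analysis, replace last observation carried forward as the primary rule. Use ANCOVA of week-4 PSS-14 on arm and baseline PSS-14, including every observed week-4 score, also those from participants who stopped stimulation, under a stated missing-at-random assumption. Multiple imputation is an option; with 20 per arm and about four values missing in each, it is not essential. Keep baseline carried forward only as a sensitivity analysis. With 16 observed per arm and missingness at random, the plan's 81% power then applies to an undiluted effect.

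The cost is a change of wording, a little more analysis work, and reliance on an assumption that the data cannot verify. The change should be made before the allocation codes are broken. If the present rule is kept, the Sample size calculation should restate power as the range above, with the assumed sham improvement and dropout shown.
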